#### Blinding

The APOSTEL 8 trial is a double-blind trial. Blinding will be retained in this follow-up study, both for patients and investigators. After completion of participation in this follow-up trial, participants will be offered information on their allocation.

### Outcomes

The primary outcomes of this follow-up study include a composite of children’s (mildly) abnormal neurodevelopment and/or behaviour problems. Secondary outcomes include child’s growth, weight and general health. We will report the outcomes as a separate outcome, as well as a composite outcome as described below. We will present data as continuous scores (with mean and SD or median with IQR) and/or as dichotomised scores (based on the predefined cut-off scores). See table 1 for an overview of the questionnaires and outcomes.

**Table 1 T1:** Overview of outcomes

Outcome	Method of measurement	Definition	Outcome measurement
Neurodevelopment	Ages and Stages Questionnaire third edition (ASQ-3)	Scores on five domains: Communication Gross motor skills Fine motor skills Problem-solving skills Personal-social skills	Mean (SD)Abnormal:≥2 SD below mean in any domain≥1 SD below mean in multiple domains*Mildly abnormal:≥1 and <2 SD below mean in one domain*
	Vineland screener	Total adaptive functioning score based on four domains: Communication Social skills Daily living skills Motor skills	Mean (SD)Abnormal:≤10th percentile of the population*Mildly abnormal:11th–25th percentile of the population*
Behaviour	Strength and Difficulties Questionnaire (SDQ)	Total difficulties score including four subscales: Conduct problems Emotional symptoms Hyperactivity Peer relationships	Mean (SD)Abnormal:>90th percentile of the population*Mildly abnormal:80th–90th percentile of the population*
Mortality	Cross-check medical files and Dutch Personal Record database	Perinatal mortality and death up to around 4 years of corrected age	Number (%)†
General health	General Health Questionnaire‡	Height	Mean (SD)Abnormal: 1.6 SD above or below target height range*
		BMI	Mean (SD)Abnormal^34 35^: underweight* overweight* obesity*
		Morbidity, medication use, hospital admissions, surgeries	Number (%)
Primary outcome	ASQ-3, Vineland screener, SDQ and mortality	Composite outcome is divided into abnormal and mildly abnormal	Abnormal:Score in ASQ-3, vineland screener or SDQ questionnaire is abnormal as defined aboveMildly abnormal:Score in ASQ-3, vineland screener or SDQ questionnaire is mildly abnormal as defined above

* Cut-off according to age and gender.The denominator changes into all children born to participants of the original APOSTEL 8 trial.

† This questionnaire was developed by our research team that is specialised in follow-up research of obstetric intervention studies. The questionnaire has been used in multiple follow-up studies.The denominator changes into all children born to participants of the original APOSTEL 8 trial.

‡ This questionnaire was developed by our research team that is specialised in follow-up research of obstetric intervention studies. The questionnaire has been used in multiple follow-up studies.^22 30 38^

APOSTEL 8Assessment of Perinatal Outcome after Specific Tocolysis in Early Labour 8BMI, body mass indexSDS, SD Score

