**Methods and analysis:**

This protocol concerns a follow-up study of the multicentre randomised double-blind placebo controlled APOSTEL 8 trial (NL61439.018.17, EudraCT-number 2017-001007-72). In this trial, women with threatened preterm birth (between 30 and 34 weeks of gestation) defined as uterine contractions with (1) a cervical length of <15 mm or (2) a cervical length of 15–30 mm and a positive fibronectin test or (3) in centres where cervical length measurement is not part of the local protocol: a positive fibronectin test or Actim-Partus test or (4) ruptured membranes, are randomised to atosiban or placebo for 48 hours. The primary outcome is a composite of perinatal mortality and severe neonatal morbidity. Children born to mothers who participated in the APOSTEL 8 study (n=760) will be eligible for follow-up at 4 years of corrected age and assessed using four parent-reported questionnaires. Primary outcomes are neurodevelopment and behaviour problems. Secondary outcomes are on child growth and general health. All outcomes will be compared between the atosiban and placebo group with OR and corresponding 95% CI. Analyses will be performed using the intention-to-treat approach.

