#### Composite outcomes

Since both behaviour and neurodevelopment are equally important, we report on a composite outcome. Composite adverse child outcome is defined as:

Abnormal adverse child outcome: if the score in ASQ-3, Vineland screener or SDQ questionnaire is abnormal as defined before.Mildly abnormal adverse child outcome: if the score in ASQ-3, Vineland screener or SDQ questionnaire is mildly abnormal as defined before.Death or survival with abnormal cognitive and/or behaviour development: abnormal adverse child outcome as defined previously or death up to 4 years after randomisation.

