### Sample size

The original APOSTEL 8 superiority trial with an aimed sample size of 760 pregnancies (of which approximately 635 singletons and 125 multiples). Since only participants of the original APOSTEL 8 trial are eligible for inclusion in this follow-up study, the maximum number of possible participants is fixed. Based on our previous follow-up studies using questionnaires, we expect to realise a follow-up rate of 50%,^20 22 36^ resulting in approximately 400 children to be included. Group sample sizes of 200 children in the atosiban group and 200 children in the placebo group achieve 80% power to detect a difference of 12% between group proportions in our composite main outcome. The test statistic used is the two-sided Z-Test with pooled variance with a significance level of the test is 0.05.

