#### Additional sensitivity analyses

In accordance with the APOSTEL 8 trial, the following subgroup analyses are planned:

Singleton and multiple pregnancy separately.Cervical length <15 mm vs cervical length 15–30 mm and a positive fibronectin test (or no

cervical length measurement and a positive fibronectin test or Partus test).

Ruptured vs intact membranes at entry.Previous preterm birth.Excluding children that exceed the optimal window of 3;9 years–4;3 years of corrected age. In sensitivity analyses, we will use imputation techniques to impute missing outcome data for children lost to follow-up. Multiple imputation techniques will only be applied when it can be assumed that data are missing at random and the follow rate is >70%. the follow-up rate is lower than 70, a best-case and worst-case scenario analyses will be performed.Composite outcome of deceased children or survived children with abnormal cognitive and/or behaviour development. Combining mortality data with survival of children with a severe developmental disability will help in providing the full scope of relevant outcomes from the start of randomisation until up to 4 years of age. The denominator in this analyses will be all children born in the APOSTEL 8 trial, instead of the number of children included in follow-up. However, this outcome has some challenges due to the high probability of loss to follow-up (as is the case in many obstetrical follow-up studies after several years), and therefore, the inevitable need to deal with missing data. This will be done by either applying multiple imputation techniques or, in case of a high loss to follow-up, a worst-case and best-case scenario analyses.

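### The protocol does not identify one primary outcome: one versus two primaries, and whether mildly abnormal scores count, are left open

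*Protocol article*

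**What the plan says.** The relevant statements in the protocol article are:

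- **Abstract, Methods and analysis:** "Primary outcomes are neurodevelopment and behaviour problems". The Statistical analysis section likewise treats neurodevelopment and behaviour as the main outcomes.
- **Outcomes, text:** "The primary outcomes of this follow-up study include a composite of children’s (mildly) abnormal neurodevelopment and/or behaviour problems". The next lines add: "We will report the outcomes as a separate outcome, as well as a composite outcome as described below".
- **Outcomes, Table 1, primary outcome row:** the measurement cell reads "ASQ-3, Vineland screener, SDQ and mortality" and the definition cell reads "Composite outcome is divided into abnormal and mildly abnormal". The two criteria that follow use questionnaire scores only.
- **Composite outcomes:** three composites are listed: abnormal on any of the three instruments; mildly abnormal on any of the three; and "Death or survival with abnormal cognitive and/or behaviour development: abnormal adverse child outcome as defined previously or death up to 4 years after randomisation". None is called primary.
- **Sample size:** 200 children per group give 80% power to "detect a difference of 12% between group proportions in our composite main outcome", with a pooled two-sided Z-test at 0.05. The section does not say which composite is meant and gives no reference rate.
- **Additional sensitivity analyses:** the list includes "Composite outcome of deceased children or survived children with abnormal cognitive and/or behaviour development", with all children born in the trial as its denominator.

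**The concern.** A protocol should let a reader say in advance which single comparison decides the study. Here a reader could choose neurodevelopment and behaviour as two primaries, the abnormal composite, or the composite that also counts mildly abnormal scores. Each choice has support somewhere in the text. An effect could then be claimed on whichever version showed one, and the power statement cannot be checked because its outcome is not named. This is not detail that a condensed article leaves to a fuller document: the article states the primary outcome several times, and the statements differ.

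**Working it through.** **1. The statements side by side**

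| Place | Number of primaries | Mildly abnormal counts? | Death counts? |
|---|---|---|---|
| Abstract; Statistical analysis | Two | Not said (abstract); both levels reported (analysis) | No |
| Outcomes text | Plural, including a composite | In brackets, so unclear | No |
| Table 1, primary row | One composite in two levels | Yes, as a separate level | Listed as input, absent from both criteria |
| Composite outcomes | Three, none called primary | Second composite only | Third composite only |
| Sample size | One, unnamed | Not said | Not said |
| Additional sensitivity analyses | Not applicable | Not in this composite | Yes, as a sensitivity analysis |

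The last row largely settles the place of the death composite. Nothing settles the other two columns.

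**2. Reproducing the stated power**

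Inputs from Sample size: n = 200 per group, difference 0.12, two-sided alpha 0.05, pooled Z-test. With p̄ the mean of the two proportions,

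power = Φ{ [0.12 − 1.96·√(2p̄(1−p̄)/n)] / √([p₁(1−p₁)+p₂(1−p₂)]/n) }.

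- 30% vs 18%: (0.12 − 1.96 × 0.04271)/0.04228 = 0.858, power 80.5%.
- 38% vs 26%: (0.12 − 1.96 × 0.04665)/0.04626 = 0.618, power 73.2%.
- 50% vs 38%: (0.12 − 1.96 × 0.04964)/0.04927 = 0.461, power 67.8%.

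The stated 80% is reproduced to within 2 points only if the lower of the two rates is about 16.7-20.3% or, by symmetry, about 67.7-71.3%. The 30% and 38% starting rates match the composite abnormal development rates that the Background gives for an earlier trial. The Sample size section does not refer to them.

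**3. How far apart the versions may lie**

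The protocol gives no rates for its own composites, so these are assumptions. Apply the Table 1 cut-offs to a reference population with normally distributed scores and a common correlation between scores:

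| Correlation | Abnormal | Abnormal or mildly abnormal |
|---|---|---|
| 0.3 | 32.6% | 60.4% |
| 0.5 | 28.8% | 51.6% |
| 0.7 | 24.8% | 42.5% |

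With uncorrelated scores the figures are 38.3% and 74.7%. Over 25-33% (abnormal), power for 12 points in either direction is about 69-87%. Over 43-60% (wider composite) it is about 67-72%. The ranges overlap, but the wider composite does not reach 80% anywhere in its range.

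Read literally, the mildly abnormal composite also takes in children who are abnormal on another instrument. About 13% of children would count in both composites in each of these scenarios.

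**4. Error rate if both nested composites were tested at 0.05**

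Every abnormal child is also a case in the wider composite. On a common denominator the two event indicators correlate at ρ = √{p_A(1−p_W)/[p_W(1−p_A)]}, and the error is 1 − P(|Z₁|<1.96, |Z₂|<1.96) for bivariate normal Z with that ρ.

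- p_A = 25%, p_W = 43%: ρ = √(0.1425/0.3225) = 0.665, error 8.5%.
- p_A = 33%, p_W = 60%: ρ = √(0.132/0.402) = 0.573, error 8.9%.
- Independent tests, as an upper bound: 1 − 0.95² = 9.75%.

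If neurodevelopment and behaviour were instead two primaries with either one sufficing, the same 9.75% bound applies. Splitting alpha to 0.025 each would lower the power for 30% vs 18% from 80.5% to 71.7%.

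**The case against.** The strongest reply is that the intention can be pieced together. The abstract may be shorthand for the composite. The Composite outcomes section says why the two areas are combined, and the sample size speaks of one main composite. Separate results may only be meant for reporting. This is a fair reading and makes a single composite the likelier intention. It still does not say whether mildly abnormal scores belong to it, and the Statistical analysis section goes back to two main outcomes.

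Several stronger inferences are tempting, and the document does not support them:

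- **That death-or-abnormal is a rival primary, so three tests give 1 − 0.95³ = 14.3%.** That composite is listed as a sensitivity analysis with its own denominator, and the outcomes are nested rather than independent. Even if it were counted, with about 2 points of deaths assumed, the error would be about 9-10.5%.
- **That the plan tests every version at 0.05.** The Sample size section ties 0.05 to the one composite. The p<0.05 sentence under Statistical analysis stands with the baseline comparisons, and outcomes are to be given as estimates with 95% confidence intervals. The error rates above are therefore conditional.
- **That a comparison among survivors contradicts the Table 1 primary row.** The criteria in that row use questionnaire scores only, and mortality is reported separately for all children born. What remains is one entry in the measurement cell.
- **That the power figure fits no version.** It fits 30% vs 18%, and 30% is one of the two rates from the earlier trial. The protocol does not make that link.

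**Conclusion.** The concern holds in this limited form: the primary outcome is not fixed. The main gaps are one versus two primaries and whether mildly abnormal scores count; the mortality entry in the Table 1 primary row is a smaller inconsistency. This rests on the text alone. The sizes rest on assumptions. The 8.5-9% requires both nested composites to be tested at 0.05 with abnormal at 25-33% and the wider composite at 43-60%. The power figures of 80.5%, 73% and 68% follow from the stated design once a rate is chosen, before any allowance for multiple pregnancies. Because the gap concerns the outcome that decides the study, it must be closed before unblinded analysis.

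**What to change.** Before unblinded analysis:

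1. Name one primary outcome. One suitable choice is the abnormal composite (abnormal on ASQ-3, Vineland screener or SDQ) at about 4 years corrected age, tested once at two-sided 0.05. Another single choice, or two primaries with a stated alpha split, would also close the gap.
2. Label abnormal-or-mildly-abnormal and the single instruments as secondary, and make the abnormal and mildly abnormal categories mutually exclusive.
3. Keep death-or-abnormal as the sensitivity analysis it already is, and take mortality out of the measurement cell of the Table 1 primary row.
4. Use the same definition in the abstract, Outcomes, Table 1, Composite outcomes, Sample size, Statistical analysis and Additional sensitivity analyses.
5. State the reference rate assumed for that outcome and the power it gives with 200 per group.

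The cost is wording. The sponsor gives up the choice among versions, and the restated power may be slightly less favourable than 80%.

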#### (Neuro)development

The third version of the Ages and Stages Questionnaire (ASQ-3) will be used to assess neurodevelopment. The ASQ-3 is a screening tool to monitor child development by measuring five domains: communication, gross and fine motor skills, problem-solving skills and personal-social skills and can be used till 6 years of age. The ASQ-3 is the most commonly used parent-reported screening tool on development worldwide and is validated in a Dutch reference population.^24^

Interpretation: scores of ≥1 SD below the mean of the ASQ normative data in two or more domains or ≥2 SD below the normative mean in at least one domain will be considered abnormal. A score of ≥1 and <2 SD below mean in one domain will be considered as mildly abnormal.

The Vineland screener is a tool developed in the Netherlands to assess adaptive functioning in children up to 6 years of age. Adaptive functions refers to how well a person copes with common demands in life. The tool consists of 72 questions concerning everyday behaviour and covers four domains: communication, social, motor and daily living skills. The total adaptive functioning score is the sum of these four domains.^25 26^

Interpretation: A score between the 11th and 25th percentile of the population is considered mildly abnormal (77–84 for children of 3–4 years of age and 100–107 for children 4–5 years of age). A score ≤10th percentile of the population is considered as abnormal (≤76 for children of 3–4 years of age, ≤99 for children of 4–5 years of age).

#### Behaviour problems

The Strengths and Difficulties Questionnaire (SDQ) will be used to assess behaviour disabilities. The SDQ is a screening tool to identify behavioural problems in children from 3 to 17 years of age and covers five domains: emotional symptoms, conduct problems, hyperactivity/inactivity, peer problems and prosocial behaviour. Apart from domain scores, a total difficulties score can be calculated including the first four domains described previously.^27 28^ The SDQ has been validated in a Dutch reference population.^29^

Interpretation: for children below 4 years of age, a Total Difficulty Score of ≥16 points is considered abnormal (>90th percentile) and a score of 13–15 points is considered mildly abnormal (80th–90th percentile). For children older than 4 years of age, a Total Difficulty Score of ≥17 is considered abnormal (>90th percentile) and a score of 14–16 points is considered mildly abnormal (80th–90th percentile).

#### Mortality

Child death (defined as perinatal mortality and death up to 4 years of corrected age). Medical records and the Dutch Personal Records Database will be used to verify the number of deceased children.

#### General health

We used a general health questionnaire to assess general health of children. This questionnaire was developed by our research team and has been used in several previous obstetric follow-up studies performed by the nationwide obstetric consortium.^30^,^32^ Questions concern child growth and health related problems (ie, need for surgery, hospital admissions, medication use and reported medical conditions).

#### Interpretation

Growth: we will present height as a continuous and dichotomous outcome (normal/abnormal score). An abnormal score is defined as 1.6 SDS above or below target height range based on parental height Dutch reference values.^33^ We will calculate the body mass index (BMI) and will report BMI as a continuous outcome and as a proportion of children who are underweight, overweight or obese based on Dutch reference data.^34 35^Health-related problems: we will report on medical conditions, hospital admissions, medication (used) and history of surgery.

#### Composite outcomes

Since both behaviour and neurodevelopment are equally important, we report on a composite outcome. Composite adverse child outcome is defined as:

Abnormal adverse child outcome: if the score in ASQ-3, Vineland screener or SDQ questionnaire is abnormal as defined before.Mildly abnormal adverse child outcome: if the score in ASQ-3, Vineland screener or SDQ questionnaire is mildly abnormal as defined before.Death or survival with abnormal cognitive and/or behaviour development: abnormal adverse child outcome as defined previously or death up to 4 years after randomisation.

### Sample size

The original APOSTEL 8 superiority trial with an aimed sample size of 760 pregnancies (of which approximately 635 singletons and 125 multiples). Since only participants of the original APOSTEL 8 trial are eligible for inclusion in this follow-up study, the maximum number of possible participants is fixed. Based on our previous follow-up studies using questionnaires, we expect to realise a follow-up rate of 50%,^20 22 36^ resulting in approximately 400 children to be included. Group sample sizes of 200 children in the atosiban group and 200 children in the placebo group achieve 80% power to detect a difference of 12% between group proportions in our composite main outcome. The test statistic used is the two-sided Z-Test with pooled variance with a significance level of the test is 0.05.

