Besides the effects on the immediate neonatal period before hospital discharge, it is essential to extend our scope on long-term child’s health and developmental outcomes since pregnancy interventions can have unexpected harmful long-term effects.^14^,^18^ However, thus far only a few randomised trials concerning tocolytic drug administration during pregnancy have performed long-term follow-up on child development. Our research group conducted the APOSTEL II trial, comparing nifedipine maintenance therapy to placebo in case of threatened preterm birth between 26 and 32 weeks of gestation.^19^ At 2 years of age, we found a higher rate of fine motor problems in the nifedipine group (n=78) (22.2% vs 7.6%), but lower rate of poor problem-solving (21.2% vs 29.1%) compared with the placebo group (n=66).^20^ We concluded that there was insufficient evidence to support use of nifedipine for maintenance tocolysis. Second, the APOSTEL III trial compared tocolysis with nifedipine versus atosiban in threatened preterm birth between 25 and 34 weeks of gestation.^21^ Follow-up at 2.5–5.5 years showed composite abnormal development in 30% of children in the nifedipine group (n=115) and 38% in the atosiban group (n=110).^22^ Neither nifedipine nor atosiban was considered as preferred treatment in women with threatened preterm birth on both short-term and long-term outcome. A recent population-based cohort study including 600 children reported no difference in neurodevelopmental outcomes at 5.5 years among children with and without antenatal exposure to tocolysis by atosiban or nifedipine. However, follow-up outcomes were retrospectively obtained and the population solely concerned pregnancies complicated by preterm prelabor rupture of membranes between 24 and 32 weeks gestation.^23^

In conclusion, long-term effects of tocolytic drug administration during pregnancy on child outcomes are still largely unknown. We will, therefore, perform a follow-up study of the randomised placebo-controlled APOSTEL 8 trial. This follow-up study aims to determine the long-term effects of atosiban versus placebo in threatened preterm birth on neurodevelopment, behaviour problems and general health of children around 4 years of corrected age. The APOSTEL 8 follow-up will help to identify potential beneficial or harmful effects of atosiban administration during pregnancy and will contribute to further improving threatened preterm birth healthcare.

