### Participants/eligibility criteria

Children of both singleton and multiple pregnancies, born to mothers who participated in the APOSTEL 8 trial, will be eligible for inclusion. Assessment will be performed when children are around 4 years of corrected age (ideally between 3 years and 9 months (3;9) to 4 years and 3 months (4;3) years of corrected age). Participants who did not give consent to be approached for follow-up research in the original APOSTEL 8 trial, will not be approached in this follow-up study. Also, participants included in the UK or Ireland will not be eligible for inclusion.

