#### Statistical analysis

Differences in baseline characteristics of APOSTEL 8 follow-up participants will be compared between atosiban and placebo group using unpaired t-test, Mann-Whitney U test, χ^2^ test or Fisher’s exact test when appropriate. A two‐sided p<0.05 will be considered statistically significant. To detect potential attrition bias, baseline characteristics of follow-up participants will be compared with those lost to follow-up.

For the main outcomes, neurodevelopment and behaviour, we will report mean scores with SD and dichotomous outcomes (abnormal/mildly abnormal) of the domains and total score of the ASQ-3, Vineland screener and SDQ. For general health-related outcomes, we will report on the outcomes as previously described. For the outcome mortality, the denominator needs to be changed into all children born to participants of the original APOSTEL 8 trial.

For the main analysis, all outcomes will be analysed using generalised linear mixed effects model to enable accounting for the dependence of multiple pregnancies. For continuous outcomes, this will provide mean difference with 95% CI and for dichotomous outcomes OR with 95% CI. All analyses will be performed according to the intention-to-treat principle and complete case analysis using SPSS or R (latest version).

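### The stated 80% power for a 12-point difference has no base rate or sibling allowance behind it, and is at most about 74% if the powered composite includes mildly abnormal scores

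*Protocol article*

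**What the plan says.** The Sample size section fixes the size, effect and test. It says that "Group sample sizes of 200 children in the atosiban group and 200 children in the placebo group achieve 80% power". The effect is an absolute gap of 12 percentage points on the main composite, and the test is a "two-sided Z-Test with pooled variance with a significance level of the test is 0.05". It states no proportion for either arm. The 400 children come from an expected 50% follow-up of a trial that aimed for 760 pregnancies, about 635 singleton and 125 multiple.

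Four other places bear on that figure:

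- The Outcomes section describes the primary composite as covering "mildly) abnormal neurodevelopment and/or behaviour problems". Under (Neuro)development, a Vineland score up to the 25th population percentile is mildly abnormal or worse.
- The Background gives the only composite rates in the document, from an earlier trial of nifedipine against atosiban: "composite abnormal development in 30% of children in the nifedipine group (n=115) and 38% in the atosiban group (n=110".
- The Statistical analysis section plans a "generalised linear mixed effects model to enable accounting for the dependence of multiple pregnancies".
- The abstract says "Children born to mothers who participated in the APOSTEL 8 study (n=760) will be eligible for follow-up at 4 years of corrected age", whereas the eligibility section says "participants included in the UK or Ireland will not be eligible for inclusion" and also leaves out mothers who did not consent to be approached for follow-up.

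**The concern.** For a fixed absolute difference, the power of a two-proportion Z-test depends on where the two proportions lie, because the binomial variance grows towards 50%. A power figure with sample size, difference, test and alpha but no base rate cannot be checked. It holds only for rates that the reader has to work out. The rate implied here sits badly with a composite that counts mild results on three instruments.

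The calculation also treats 400 children as independent, while the analysis section models siblings as dependent. Mothers were randomised, so twins share an arm and their correlation widens the standard error.

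The number of children is fixed by the parent trial, and the follow-up aims to identify harm as well as benefit. A null result would be read against an 80% chance of detecting 12 points that the design may not have.

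**Working it through.** **Inputs.** From the Sample size section: n = 200 per arm, d = 0.12, two-sided alpha 0.05, pooled variance, 635 singleton and 125 multiple pregnancies. From (Neuro)development: Vineland mild-or-worse at or below the 25th percentile. From the Background: 30% and 38%. Assumed, because the document gives no value: all multiples are twins, both twins respond, and the within-pair correlation (ICC) is 0.1 to 0.5.

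**Formula.** With p̄ = (p1 + p2)/2, SE0 = √[2p̄(1−p̄)/n] and SE1 = √[(p1(1−p1) + p2(1−p2))/n], power = Φ[(d − 1.96·SE0)/SE1].

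**Step 1: reproduce the 80%.** At 18% vs 30%, p̄ = 0.24, SE0 = 0.0427 and SE1 = 0.0423. Power = Φ[(0.12 − 0.0837)/0.0423] = Φ(0.858) = 80.5%. Power is within 2 points of 80% for a lower-arm rate of 16.7% to 20.3%, and by symmetry near 70% vs 82%. Rarer outcomes give more: 15% vs 27% gives 84.1% and 10% vs 22% gives 90.8%.

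**Step 2: composite including mild results.** A child who is mildly abnormal or worse on the Vineland is already in the composite. A reference population therefore contributes about 25% before the SDQ and the five ASQ-3 domains are added. At 25% vs 37%, p̄ = 0.31, SE0 = 0.0462 and SE1 = 0.0459. Power = Φ[(0.12 − 0.0906)/0.0459] = Φ(0.640) = 73.9%. It falls further as the rates rise towards 50%, to a minimum of 67.1% at 44% vs 56%.

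**Step 3: the 38% from the Background, and siblings.** At least 635 + 2 × 125 = 885 children are expected, of whom 250 (28%) are in pairs. The design effect is 1 + 0.2825 × ICC, which is 1.028, 1.085 and 1.141 at ICC 0.1, 0.3 and 0.5. The effective n per arm is then 194.5, 184.4 and 175.2.

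| Rates | Independent | ICC 0.1 | ICC 0.3 | ICC 0.5 |
|---|---|---|---|---|
| 18% vs 30% | 80.5% | 79.4% | 77.2% | 75.1% |
| 25% vs 37% | 73.9% | 72.7% | 70.4% | 68.2% |
| 26% vs 38% | 73.2% | 72.0% | 69.6% | 67.4% |
| 38% vs 50% | 67.8% | 66.5% | 64.2% | 62.0% |

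**Step 4: difference detectable at 80% power.** Solving the same formula for d, measured upwards from the lower arm, gives 13.1 points from 26%, 13.5 from 30%, 13.9 from 38% and 14.0 from 44% with independent children. At ICC 0.5 these become 14.0, 14.4, 14.9 and 14.9.

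**Step 5: the 400.** Half of 760 is 380, and half of 885 is about 443. Neither is 400. Taking off an assumed 10%, 20% or 30% as ineligible leaves 398, 354 or 310.

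**The case against.** The 80% is attainable, so no stated number is shown to be impossible. The sample-size section adopts no event rate. A reader might infer that the plan's own rates imply 60% to 75% power, but the document does not support that. The 30% and 38% are background from another trial, in women at 25 to 34 weeks rather than 30 to 34, with a composite whose definition is not shown. The rate here could be lower, which would raise power, and the 30% taken as the higher arm gives the stated 80%. This stands.

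The 25% floor applies only if mild results count in the powered outcome. Table 1 and the Composite outcomes section define abnormal and mildly abnormal composites separately, and the sample-size section says only that a main composite is powered. The floor also assumes that neither arm falls below the reference rate. At 13% vs 25%, SE0 = 0.0392, SE1 = 0.0388 and power = Φ(1.11) = 86.7%. This stands as a condition on the result. It is also why the composite and the rate need to be named.

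The ICC is assumed, and the base rate matters more than the twins. Half of 885 children would be about 221 per arm, which at ICC 0.5 gives 79.2% at 18% vs 30% and partly offsets the twin loss. A reader might also infer that the 400 ignores the UK, Irish and consent exclusions. Since 400 matches neither 380 nor 443, and is close to the 398 left after a 10% deduction, the documents do not show this. They show only that the derivation is not given.

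Finally, results will be reported with 95% confidence intervals, so a null finding can be read from its interval. That lessens the harm but does not make the printed power correct.

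**Conclusion.** The point holds in a conditional form. The 80% is stated without qualification, but with 200 independent children per arm it needs a lower-arm rate of about 18% or less, or rates near 70% vs 82%.

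- If the composite includes mild results, and neither arm lies below the reference rate or in the high range just named, power is at most about 74%.
- If the atosiban rate is 38%, power is 73% or 68%, depending on whether atosiban is the higher or the lower arm.
- Twin dependence lowers each figure by about 1 to 6 points for an assumed ICC of 0.1 to 0.5.

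The independence assumption conflicts with the article's own analysis model, and the abstract's eligibility statement conflicts with the eligibility section. The documents do not establish a single true power, and they do not show that the 400 was computed without the exclusions.

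**What to change.** Restate the sample-size paragraph so that it:

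- names the composite that is powered (abnormal only, or abnormal plus mildly abnormal);
- gives the assumed placebo rate and its source;
- applies a design effect for multiples, with the assumed ICC stated and varied;
- shows how 400 follows from the eligible Dutch children whose mothers agreed to re-contact;
- reports the resulting power, or the difference detectable at 80% power, for an increase and for a decrease. For lower-arm rates of roughly 26% to 44% this is about 13 to 15 points.

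Align the abstract's statement that children from all 760 are eligible with the eligibility section.

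The cost is one rewritten paragraph and one corrected sentence. No extra recruitment or change of analysis is needed. The stated power will probably be less favourable.
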